### Study and aims

We hypothesize that Tafamidis could improve microvascular dysfunction in patients suffering from ATTR cardiomyopathy, quantifiable with MBF and MFR. This could result into a MBF and MFR improvement at the evaluation after 24 months of treatment, in comparison with baseline. The second minor objective is to confirm the microvascular dysfunction described in PET by Dorbala et al., using dynamic SPECT.

## Methods and analysis

### Study protocol

This is a multicentric, prospective, observational cohort study involving three French academic hospitals (University Hospital of Angers, University Hospital of Tours and Regional Hospital of Orleans). Study patients will enter the cohort after they have been diagnosed with cardiac ATTR, including ^99m^Tc-PYP scintigraphy (grade 2 or 3) (20–22), according to the diagnostic algorithm for cardiac ATTR proposed by Gillmore et al., after they meet inclusion/exclusion criteria (Table 1).

**TABLE 1 T1:** Inclusion and exclusion criteria.

Inclusion criteria	Exclusion criteria
● Patients aged from 18 to 90 years	● Other heart failure cause (not ATTR)
● Understanding and speaking French ● With TTR amyloid cardiomyopathy (ATTRxt or ATTRm) confirmed by the association of: ⚬ clinical heart failure (NYHA I-III) ⚬ with echocardiogram and/or magnetic resonance imaging suggesting/indicating cardiac amyloidosis, ⚬ grade 2 or 3 99mTc PYP or bone scintigraphy, ⚬ and negative biological findings (i.e., serum immunofixation, urine immunofixation, serum free light chain assay), or, if one of those criteria is not met, amyloid deposits on biopsy specimens (from cardiac and non-cardiac sites), ● Intention to treat (Tafamadis)	● New York Heart Association (NYHA) class IV heart failure. ● Light-chain amyloidosis ● Liver or heart transplantation history ● Glomerular filtration rate below 25 mL per minute per 1.73 m^2^ of bodysurface area (Cockroft) ● High liver transaminase levels (two times the upper limit of the normal range) ● Severe malnutrition defined by a modified body-mass index (mBMI: serum albumin level in grams per litter multiplied by the conventional BMI) of less than 600; ● Concurrent treatment with non-steroidal anti-inflammatory drugs, tauroursodeoxycholate, doxycycline, calcium-channel blockers, digitalis, or ticagrelor ● Previous treatment with tafamidis or patisaran ● Previous CAD, severe epicardial stenosis with revascularization or ticagrelor treatment, coronary artery bypass grafting, myocardial infarction ● Contra-indications to pharmacological stress testing MPI: severe hypotension (<90 mmHg of Systolic arterial pressure), atrioventricular block 2nd or 3rd grade, carotid stenosis (unilateral > 70%, bilateral > 50%) ● Pregnancy ● Breastfeeding ● Protected adults

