New therapeutic options are arising in cardiac ATTR. In a multicentric, international, double-blind, placebo-controlled, phase 3 trial, including 441 patients with ATTR cardiomyopathy, Maurer et al. showed that Tafamidis (80 mg and 20 mg) was associated with reductions in all-cause mortality (78 of 264 [29.5%] vs. 76 of 177 [42.9%]; hazard ratio, 0.70; 95% confidence interval [CI], 0.51–0.96) and cardiovascular-related hospitalizations after 18 months [relative risk ratio of 0.68 (0.48 per year vs. 0.70 per year; 95% CI, 0.56–0.81)], and reduced the decline in functional capacity and quality of life after 6 months as compared with placebo in patients with transthyretin amyloid cardiomyopathy (15). Tafamidis has now been approved for patients with ATTR cardiomyopathy and is recommended class I in the latest European guidelines on heart failure (16).

In APPOLO trial (international, randomized, double-blind, placebo-controlled phase 3 trial with hereditary ATTR amyloidosis), Patisaran, by stopping the synthesis of TTR through gene silencing, decreased mean left ventricular wall thickness, global longitudinal strain, N-terminal prohormone of brain natriuretic peptide, and adverse cardiac outcomes compared with placebo at month 18 (17). Authors used Patisaran 0.3 mg/kg IV once every 3 weeks in 225 ATTR-FAP patients. Others pharmacological trials explored Inotersen treatment (gene silencer too), but they focused on neurological disease: NEURO-TTR phase 3 trial (18).

About others tetramer stabilizers, no beneficial cardiac effect has been shown in Diflunisal treatment, and a randomized double-blind, placebo-controlled Phase 2 trial has been initiated, as mentioned in a recent mini review (19).

To our knowledge, no study focused on the effect of cardiac amyloidosis treatment on microvascular dysfunction.

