We might also consider a significant improvement of MFR after treatment. This would confirm a potential pathophysiological mechanism of the clinical improvement obtained by Tafamidis. It would then be interesting, in a second study, to evaluate whether this improvement in coronary microcirculation occurs early, within the first 12 months. Indeed, there is a need for biomarkers to predict the response to Tafamidis. Some will not respond to therapy; Monteiro et al. built a model to predict responsiveness to Tafamidis (31). They identified that disease severity, sex, and native TTR concentration at the outset of treatment were the most relevant predictors of response to Tafamidis. Plasma Tafamidis concentration after 12 months of therapy was also a predictor of response for male patients. Falk et al. suggested that measurement of TTR level change post-Tafamidis might be a surrogate for stabilization and could be an accurate measure of drug efficacy (32). Other treatments such as RNA interference therapeutics are developing rapidly in this indication with, it seems for the moment, great efficacy (17). So, the idea of a biomarker, possibly early, of efficacy would make it possible to quickly orient patients labeled as non-responders toward a switch to another therapy or to an association (combo RNAi and Tafamidis).

Finally, we might also envisage a lack of significant change in MFR values between 0 and 24 months. Our primary hypothesis would be untested. The potential limitations of our study would be a too short follow-up, or a too small sample.

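### Table 1 bars earlier tafamidis and patisiran but not inotersen or earlier diflunisal, and a TTR drug started later stays in the change read as the Tafamidis effect

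*Protocol article*

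**What the plan says.** Two exclusion lines in Table 1 (section Study protocol) bear on other drugs. One concerns earlier TTR-directed therapy: "Previous treatment with tafamidis or patisaran". The other concerns drugs being taken at entry: "Concurrent treatment with non-steroidal anti-inflammatory drugs, tauroursodeoxycholate, doxycycline, calcium-channel blockers, digitalis, or ticagrelor".

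The section Current knowledge names two further TTR drugs. On silencers: "Others pharmacological trials explored Inotersen treatment (gene silencer too), but they focused on neurological disease". On stabilisers: "About others tetramer stabilizers, no beneficial cardiac effect has been shown in Diflunisal treatment".

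Hereditary disease is eligible, since the inclusion criterion reads "With TTR amyloid cardiomyopathy (ATTRxt or ATTRm) confirmed by the association of".

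The primary outcome (Trial outcomes) is the change in stress and rest myocardial blood flow and flow reserve from baseline to 24 months. The abstract says the Tafamidis effect will be assessed by intention to treat. The Discussion acknowledges that there is no control population. For follow-up, Interventions and participant timeline lists interruptions of treatment and hospital admissions among the clinical data. It does not mention the start of another TTR drug.

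**The concern.** The evident purpose of the earlier-treatment line is a baseline scan not yet affected by TTR therapy, so that the later change can be read as that of Tafamidis. A list of two drugs serves that purpose only if no other drug of the same kind is in play, and the article itself names two more.

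Without a comparator, eligibility and handling rules are the main protection for the attribution. A patient on inotersen at entry has a treated baseline. That touches the secondary aim of confirming reduced flow at baseline as well as the primary change. A patient who starts another TTR drug after baseline has a 24-month scan that reflects both drugs, and nothing in the design can separate them.

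The article accepts this reasoning elsewhere. Patients with epicardial stenosis are analysed apart, because revascularisation or ticagrelor might alter flow reserve. No parallel rule is stated for a second drug acting on the disease pathway under study.

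**Working it through.** No figure in the article depends on this criterion, and the sample size of 50 comes without a calculation, so there is no stated number to reproduce. The check is a comparison of Table 1 with the TTR drugs named in Current knowledge, followed by an illustration of size.

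**Drug by drug**

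| Drug | Class in the article | Previous use | Ongoing at entry | Started after baseline |
|---|---|---|---|---|
| Tafamidis | stabiliser | excluded | excluded (as previous use) | study treatment |
| Patisiran | gene silencer | excluded | excluded (as previous use) | no rule stated |
| Inotersen | gene silencer | not excluded | not excluded | no rule stated |
| Diflunisal | stabiliser | not excluded | excluded only if read as an NSAID; the article does not say so | no rule stated |

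The open cells at entry are inotersen (both columns) and previous diflunisal. The last column is open for every drug except the study treatment.

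**Illustrative size**

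Inputs from the article: n = 50 and a two-tailed paired t-test. Assumed inputs: two-sided alpha 0.05; all 50 patients have both scans; k patients are affected by another TTR drug; each of these has an extra change of d, in SD units of the paired change; the SD itself is unaffected. The article gives neither k nor d.

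Change detectable with 80% power: (1.960 + 0.842)/√50 = 2.802/7.071 = 0.396 SD by the normal approximation, or 0.404 SD with the t distribution.

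Shift in the mean change = (k/50) × d. The last column below is the probability of a significant result if Tafamidis itself changes nothing.

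| k | d | Shift (SD) | Rejection probability |
|---|---|---|---|
| 1 | 0.25 | 0.005 | 0.050 |
| 1 | 1.0 | 0.02 | 0.052 |
| 2 | 0.25 | 0.01 | 0.051 |
| 2 | 1.0 | 0.04 | 0.059 |
| 5 | 0.25 | 0.025 | 0.053 |
| 5 | 1.0 | 0.10 | 0.107 |
| 10 | 0.25 | 0.05 | 0.064 |
| 10 | 1.0 | 0.20 | 0.284 |

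With one or two affected patients the shift is at most 0.04 SD, about a tenth of the detectable change (0.04/0.404 = 0.10). With five it is at most 0.10 SD, about a quarter (0.10/0.404 = 0.25). Only a sizeable share of the cohort would matter numerically.

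**The case against.** Several arguments limit the point, and most of them stand.

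- **Entry pathway.** Patients are pre-screened when referred for the diagnostic scan, and are included and started on Tafamidis once the diagnosis is confirmed. Most therefore enter at first cardiac diagnosis, when earlier TTR therapy is unlikely. The gap concerns mainly hereditary patients already treated for another manifestation.
- **Evidence of a cardiac effect.** A reader might infer that the silencer benefit reported at month 18 applies to patients admitted through this gap. It does not: that result is for patisiran, which is barred at entry. For diflunisal the article states "no beneficial cardiac effect has been shown in Diflunisal treatment", and it describes the inotersen trials as neurological. The patisiran result is relevant only to a start after baseline, which a line on previous treatment does not reach.
- **Stable earlier treatment.** A drug already being taken is reflected in the baseline scan, so it need not bias the within-patient change.
- **Concurrent drugs.** A reader might infer that other anti-amyloid agents can be taken freely at entry. The concurrent-drug line bars doxycycline and tauroursodeoxycholate, and the article does not present either as a TTR drug.
- **Planned switching.** A reader might take the Discussion's phrase "toward a switch to another therapy or to an association (combo RNAi and Tafamidis" as a sign that this cohort will switch. It describes what a future early biomarker might allow, and is not a plan for these patients.
- **Intention to treat and unseen documents.** Keeping switchers in the main analysis follows from the declared approach. Data management says treatment details are collected, and detailed handling rules may stand in the full protocol or analysis plan.

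What survives is the stated criterion. It samples two drug classes and leaves out the other member of each that the article names.

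**Conclusion.** The point holds as a minor one. Table 1 leaves eligible patients with previous or ongoing inotersen, or with previous diflunisal. Ongoing diflunisal is barred only through a site's reading of the NSAID line. A TTR-directed drug begun during the 24 months stays in a before-after change described as the effect of Tafamidis, and no control group can separate it.

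The size cannot be derived from the document, which gives neither the hereditary share nor any rate of use of other TTR drugs. The illustration rests wholly on assumed k and d and suggests little distortion for a handful of patients. A reader might conclude that the primary result would be materially biased, but nothing in the document supports that. The gain from a change is clearer interpretation. The absence of a control group remains the larger limit on attribution, and rewording this criterion does not remove it.

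**What to change.** 1. Reword the eligibility line by class: previous or current treatment with any TTR stabiliser or TTR gene silencer, with tafamidis, diflunisal, patisiran and inotersen as named examples.
2. Record in the electronic case report form the start date of any such drug, other than the study treatment, during follow-up.
3. Keep the intention-to-treat analysis as the main one, and add a sensitivity analysis of the 24-month change without patients who added or switched to such a drug. Because this removes patients on the basis of a post-baseline event, it should be read beside the main result and should not replace it.

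This is not a rule for care: treatment decisions stay with the treating physician.

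The cost is one reworded line, one form field and one extra analysis. The downside is that a few hereditary patients may become ineligible. Recruitment opened in February 2022, so the reworded line could apply only to later inclusions. The date field and the sensitivity analysis can cover everyone, and patients already included with such exposure can be listed.

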### Inclusion and exclusion criteria

Criteria are summarized in Table 1.

### Consent

Patients who meet all inclusion criteria and none of the exclusion criteria will be offered the opportunity to participate in the study and provided with all the relevant information verbally and in writing.

The free and informed consent, in writing, of the potential participant will be obtained by the investigator before the inclusion of this person in the research.

### Interventions and participant timeline

The schedule of participants’ enrolment, interventions and assessments are presented in Figure 1.

**FIGURE 1 F1:**
[figure not shown]
Flow of the participants throughout the study. MBF, Myocardial Blood Flow; MFR, Myocardial Flow Reserve.

Potential participants referred for ATTR bone or PYP scan will be pre-screened by the nuclear medicine physician. After confirmation of TTR cardiac amyloidosis diagnosis, including ^99m^Tc-HDP or ^99m^Tc-PYP scintigraphy (grade 2 or 3) (20, 22, 23) according to the diagnostic algorithm for cardiac ATTR amyloidosis proposed by Gillmore et al., patients will be included and Tafamidis introduced, according to the guidelines. The treatment will be fully reimbursed by health insurance in this indication.

We estimate that the recruitment will take around 12–24 months. Participants will not receive any financial or non-financial incentives.

Patients will be included before the baseline dynamic CZT-SPECT myocardial perfusion imaging (with MBF and MFR), after written consent. Dynamic SPECT imaging protocol is displayed in Figure 2. All acquisitions will be performed on the same system: Discovery NM530c cardiac CZT cameras (General Electric Healthcare, Haifa, Israel) in all departments. The radiopharmaceutical used will be either ^99m^Tc-tetrofosmin for Orleans and Tours, and ^99m^Tc-mibi for Angers. Initial injection of 37 MBq will be used to center the patient’s heart in the field of view. Rest dynamic acquisition will then be performed with an injection of 250MBq of ^99m^Tc radiopharmaceutical, then flushed by 50 mL of saline to ensure consistent delivery of a tight bolus. Stress will then be induced using either a regadenoson (400 μg) injection or a dipyridamole perfusion (0.56 mg/kg), immediately followed with a 500MBq of ^99m^Tc radiopharmaceutical injection at hyperemia peak. Dynamic SPECT data will be reconstructed using Corridor 4DM™ software (INVIA, Ann Arbor, MI, United States) on a Xeleris workstation (General Electric Healthcare, Haifa, Israel).

**FIGURE 2 F2:**
[figure not shown]
Dynamic scintigraphy protocol.

Epicardial obstructive CAD will be ruled out in subjects with pathological initial imaging (coronary angiography or cardiac CT depending on the cardiologist choice). Patients with epicardial stenosis will be analyzed apart, especially if revascularization or ticagrelor treatment is performed.

Visits are mainly already included in the cardiologic follow-up of the Tafamidis treatment at 6, 12, 18, and 24 months (with cardiac echography at 12 and 24 months). Clinical data and echocardiography findings will be resumed. Clinical data will include blood pressure, NYHA class, Kansas City Cardiomyopathy Questionnaire-Overall Summary (KCCQ-OS), 6-min walking test, electrocardiogram, any treatment interruption, or hospitalization. Cardiac echography will include at least: left ventricles volumes measurement, ejection fraction, wall thickness, strain results.

Last evaluation will be CZT SPECT MPI after 24 months of treatment, in the same conditions as baseline.

### Trial outcomes

The primary outcome is the variation of stress and rest MBF and MFR assessed by dynamic SPECT, between baseline and 24 months after Tafamidis treatment.

The secondary outcomes are:

•Results from baseline dynamic SPECT, confirming the stress and rest MBF and MFR reduction in cardiac ATTR patients,•Results from echo/MRI.

### Statistical analysis plan

Interim analysis is planned after all inclusions for MBF and MFR baseline evaluation. Final analysis is planned after completion of study. A subgroup with patients suffering from CAD, assessed by invasive coronary angiography or cardiac-CT after baseline SPECT will be analyzed apart.

All MBF and MFR values will be described as mean ± SD. Normal distribution of the value will be evaluated. Comparisons between continuous variables will be performed using two-tailed paired *t*-test. Non-parametric variables will be listed as medians and compared using the Mann–Whitney *U* test. Discrete variables will be described as proportions and compared with the chi-square test. Correlations will be performed using Pearson R or non-parametric methods (Spearman rho) as indicated. Multivariable linear regression analyses will be performed to study the independent contributions of various parameters on stress MBF and MFR.

The total number of patients expected in this “proof of concept” study is 50 patients. In the context of a pilot study, the workforce calculation is not applicable, as frequently in the case of exploratory studies on innovative technologies (24). This number of patients is also compatible with the recruitment capacities of the three investigative centers.

### Data management

Data will be collected electronically including eligibility, baseline clinical, biological and imaging characteristics, treatment and outcome details. Every site will have access to the electronic case report forms *via* a web-based data collection system created using EOL (developed by Medsharing). Investigators will be given instructions for using this tool.

All trial documents will be archived and securely kept for 15 years after study completion.

### Trial organization structure

The Centre Hospitalier d’Orléans will be the sole sponsor of this multi-center study and will ensure the safety and respect of individuals who have agreed to participate in the trial. The sponsor has a quality assurance system in place to monitor the implementation of the study at the research centers.

Clinical Research Associates (CRA) will be appointed by the sponsor. After an initial visit, their main role will be to make regular follow-up visits at the different study sites.

The purpose of study monitoring, as defined in the Good Clinical Practices (GCP section 5.18.1), is to verify that:

•Research subjects are safe, protected, and their rights are respected.•The data recorded are accurate, complete, and consistent with the source documents.•The study is conducted in accordance with the current version of the protocol, GCP and all legal and regulatory requirements.

For this study, the appropriate monitoring level was determined based on the complexity, impact, and budget for the study. Therefore, the sponsor, in agreement with the coordinating investigator, agreed on a logistical score and impact and the corresponding study monitoring level of: A level.

A CRA assigned by the sponsor will oversee the proper conduct of the study, the collection, documentation, recording, and reporting all handwritten data, in accordance with the Standard Operating Procedures applied within the research center and in accordance with Good Clinical Practice and legal and regulatory requirements.

The investigator and his/her team agree to be available for regular Quality Control visits by the CRA. During these visits, the following points will be examined: written consent, compliance with the study protocol and its procedures, quality of the data collected in the case report forms: accuracy, missing data, consistency of the data with the “source” documents (medical files, appointment books, original copies of laboratory results, etc.), management of the treatments used.

### Confidentiality statement

Confidential trial data will be stored in accordance with the General Data Protection Regulation 2018. Patients will only be identified using only their date of birth and unique trial ID number.

The processing of personal data for this research falls under the scope of the provisions of Articles 53–61 of the Law of January 6, 1978 relating to information technology, data files and privacy, modified by Law No. 0204-801 of August 6, 2004.

All personal data for this trial will be processed in accordance with Chapter IX of the amended French Data Protection Act of January 6, 1978 (articles 53–61).

### Trial status

Recruitment for the trial has been opened in February 2022.

## Discussion

AMYTRE study aims to evaluate a potential effect of Tafamidis treatment on microvascular dysfunction in patients with cardiac ATTR, assessed by dynamic SPECT.

As we previously described, microvascular dysfunction has been found using PET (4), but never confirmed with dynamic SPECT. Dynamic CZT myocardial SPECT has now become a more available tool, showing similar results to PET in terms of MFR evaluation (8–11).

A potential bias in this study will be the finding of authentical CAD after initial SPECT. In this case, as described, patients will undergo coronary angiography or cardiac CT. If an epicardial stenosis is found, and requires treatment, patient will be analyzed in a subgroup. Indeed, MFR might be affected by revascularization or ticagrelor. Aikawa et al. reported in a prospective multicentric observational PET ^15^O-water study a significant improvement of PET MFR 6 months after percutaneous coronary intervention (PCI) or coronary artery bypass grafting (CABG) in patients with abnormal baseline MFR (<2.0), but no significant effect of optimal medical therapy alone (25). Driessen et al. also confirmed a significant improvement of stress MBF assessed by ^15^O-water PET in patients with PCI, even superior compared with CABG (12). Other studies showed an increase of global and regional MBF and MFR in CAD patients treated with ticagrelor when compared to clopidogrel (26, 27).

The other potential bias are diabetic patients. It has been extensively reported that diabetic patients can have microvascular dysfunction, resulting in reduced stress MBF and MFR (28, 29). Clinical informations about diabetic patients (time of evolution, known complications such as diabetic nephropathy, retinopathy…) will be collected, to better rule out any potential confounding factor.

With this study, we aim to demonstrate an impact of Tafamidis on microvascular dysfunction. Regarding our secondary endpoint, various perspectives can be seen. Firstly, the absence or low proportion of microcirculatory dysfunction in patients with cardiac amyloidosis. However, the sample size remains small, and the evaluation may be too early compared with the diagnosis (although often late); this is therefore a possible limitation of our study, which may explain the failure to find this microcirculatory dysfunction. The second option is a high proportion of microcirculatory dysfunction in patients with cardiac amyloidosis. Our hypothesis would then be confirmed and will therefore be in line with the study of Dorbala et al. performed in PET (4). Other studies also found microcirculatory dysfunction in these patients, as well as in other infiltrative heart diseases such as sarcoidosis (30), which reinforces the probability of this option.

Regarding the variation in MFR values after treatment, the first possibility is a significant decrease of MFR. In this case, the primary hypothesis of an improvement in microcirculatory dysfunction after treatment with Tafamidis would then not be verified. Thus, the lack of effect of Tafamidis on microcirculatory damage would be considered, and the benefits on overall survival, quality of life and cardiovascular events mentioned in the previous studies would probably be due to another pathophysiological process. However, an aggravating factor of Tafamidis on microcirculatory function could not be raised in our study in the absence of a “control” population (untreated or benefiting from another treatment), so another study with this objective could be envisaged, in order to distinguish the natural evolution of the pathology from a treatment effect.

We might also consider a significant improvement of MFR after treatment. This would confirm a potential pathophysiological mechanism of the clinical improvement obtained by Tafamidis. It would then be interesting, in a second study, to evaluate whether this improvement in coronary microcirculation occurs early, within the first 12 months. Indeed, there is a need for biomarkers to predict the response to Tafamidis. Some will not respond to therapy; Monteiro et al. built a model to predict responsiveness to Tafamidis (31). They identified that disease severity, sex, and native TTR concentration at the outset of treatment were the most relevant predictors of response to Tafamidis. Plasma Tafamidis concentration after 12 months of therapy was also a predictor of response for male patients. Falk et al. suggested that measurement of TTR level change post-Tafamidis might be a surrogate for stabilization and could be an accurate measure of drug efficacy (32). Other treatments such as RNA interference therapeutics are developing rapidly in this indication with, it seems for the moment, great efficacy (17). So, the idea of a biomarker, possibly early, of efficacy would make it possible to quickly orient patients labeled as non-responders toward a switch to another therapy or to an association (combo RNAi and Tafamidis).

Finally, we might also envisage a lack of significant change in MFR values between 0 and 24 months. Our primary hypothesis would be untested. The potential limitations of our study would be a too short follow-up, or a too small sample.

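### The Discussion reads a significant fall in MFR as pointing to no Tafamidis effect and another mechanism, but applies its no-control caveat only to harm; the improvement reading has the same gap

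*Protocol article*

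**What the plan says.** The design is stated under Study protocol: "This is a multicentric, prospective, observational cohort study involving three French academic hospitals". All patients are to receive Tafamidis, and no comparator is described. The section on trial outcomes defines the endpoint as follows: "The primary outcome is the variation of stress and rest MBF and MFR assessed by dynamic SPECT, between baseline and 24 months after Tafamidis treatment". For the test, the Statistical analysis plan section says "Comparisons between continuous variables will be performed using two-tailed paired" t-tests, and gives the size: "The total number of patients expected in this “proof of concept” study is 50 patients". The same section declares a sample size calculation not applicable. The hypothesis, under Study and aims, is that myocardial blood flow and MFR improve against baseline.

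The Discussion then goes through the possible results. For a significant decrease of MFR it takes three steps:

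1. The improvement hypothesis is not verified.
2. "Thus, the lack of effect of Tafamidis on microcirculatory damage would be considered".
3. The benefits on survival, quality of life and events seen in earlier studies "would probably be due to another pathophysiological process".

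The next sentence says that an aggravating effect of Tafamidis could not be raised, because there is no control population, and that another study could be envisaged "in order to distinguish the natural evolution of the pathology from a treatment effect".

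For a significant improvement, the Discussion says that this would confirm a potential mechanism of the drug's clinical benefit. No caveat about the missing control group is attached to that statement.

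**The concern.** Step 1 is sound. Steps 2 and 3 do not follow from it, and the article itself gives the reason. If natural evolution and treatment effect cannot be told apart, the data cannot show harm, but they cannot show absence of effect either. The caveat is applied to one reading of a decrease and not to the other.

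At stake is what may be concluded on a component of the primary outcome. If MFR falls and the report follows this text, it would suggest that Tafamidis does not act on the microcirculation and that its benefit arises elsewhere. If MFR rises, the report would credit the drug with a mechanism. The design supports none of these statements.

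Under Current knowledge, the article describes one established benefit of the drug in relative terms: it "reduced the decline in functional capacity and quality of life after 6 months as compared with placebo". That finding concerns function and quality of life, not MFR. It does show why a benefit need not appear as a gain over baseline.

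**Working it through.** **Stated figure.** There is none to reproduce. The article gives no power, alpha, effect size or SD of change. The check is therefore one of logic, followed by an illustration on assumed values.

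**Logic.** Write the observed mean change as

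observed change = natural change + treatment effect.

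The study measures the left side only. Both terms on the right are unknown, so treatment effect = observed change − natural change is not identified. Take an observed MFR fall of 0.25 (assumed):

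| Untreated change (assumed) | Implied treatment effect | Reading |
|---|---|---|
| −0.50 | −0.25 − (−0.50) = +0.25 | slowed decline (benefit) |
| −0.25 | −0.25 − (−0.25) = 0 | no effect |
| 0 | −0.25 − 0 = −0.25 | harm |

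The same data fit all three rows. The argument also runs the other way: a rise from baseline equals a treatment effect only if the untreated change is known to be zero.

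**Statistical significance does not help.** With n = 50 (Statistical analysis plan section) and a two-sided 5% paired t-test (5% assumed), the smallest significant fall is t(0.975; 49) × SD/√50 = 2.01 × SD/7.07. For an assumed SD of change:

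| SD | Smallest significant fall | t for a fall of 0.25 | p |
|---|---|---|---|
| 0.4 | 0.11 | −4.42 | < 0.001 |
| 0.6 | 0.17 | −2.95 | 0.005 |
| 0.8 | 0.23 | −2.21 | 0.032 |

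A fall of 0.25 is significant in each case, and the table of three readings is unchanged.

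**How often could a beneficial drug give a significant fall?** Assume an untreated 24-month MFR loss L, a drug that truly halves it (true change −L/2), and an SD of change S. The probability of landing in the lower rejection region comes from the non-central t distribution with non-centrality −(L/2)√n/S. For example, L = 0.30, S = 0.5 and n = 50 give −0.15 × 7.07/0.5 = −2.12. The 35-pair column is an assumed allowance for attrition; the article gives only 50.

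| L | S | 35 pairs | 50 pairs |
|---|---|---|---|
| 0.05 | 0.5 | 5% | 5% |
| 0.10 | 0.5 | 8% | 10% |
| 0.20 | 0.6 | 16% | 21% |
| 0.30 | 0.5 | 41% | 55% |
| 0.40 | 0.5 | 63% | 79% |
| 0.60 | 0.4 | 99% | nearly 100% |

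The result depends almost entirely on L, which the document does not supply.

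**The case against.** The strongest case on the other side has four parts.

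- **The wording is hedged.** Lack of effect would only be considered, and the other mechanism is only probable. This is a survey of possible results in a Discussion, not a decision rule, and the Statistical analysis plan section contains no such inference. This stands. A reader might infer that the plan commits in advance to declaring Tafamidis ineffective if MFR falls; the text does not say so. What remains is that a probability is attached to a mechanism on which the data carry no information, and that lack of effect is offered as the consequence of a fall.

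- **The limitation is acknowledged in the same paragraph.** This is partly right. The authors have not overlooked the missing control group, and the reason they give is general. But the sentence applies it to harm only and does not withdraw the reading that precedes it.

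- **Lack of effect may simply mean no improvement over baseline.** That would be harmless if the text stopped there. The further step to another process behind the clinical benefits makes sense only as a statement about the drug's causal effect.

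- **The size is not established.** This stands. A reader might infer that a drug that halves the loss would often be called ineffective. That needs a substantial natural fall in MFR, which the document does not report. Nor can the placebo-controlled result on function and quality of life be carried over to MFR: the article itself says that, to its authors' knowledge, no study has looked at treatment of cardiac amyloidosis and microvascular dysfunction.

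**Conclusion.** The point holds as an error of interpretation in the Discussion, not as a fault in the choice of analysis. A significant fall in MFR would leave the hypothesis of improvement over baseline unsupported. In this single-cohort design it cannot go on to indicate lack of effect, slowed decline, harm, or where the clinical benefit comes from. The improvement branch has the same defect in the favourable direction, and the two should be corrected together.

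This conclusion rests only on the design and on the article's own caveat; it needs no numerical assumption. The probabilities of a misleading significant decrease, from about 5% with a negligible natural loss to nearly 100% with a large one, are illustration only. They assume a halving effect, an SD of change of 0.4 to 0.6 and a two-sided 5% test.

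**What to change.** In the Discussion:

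- Keep the statement that, after a significant decrease, the improvement hypothesis is not verified.
- Delete the inference to lack of effect and the inference that the known benefits come from another process.
- Insert wording such as: *Because there is no control group, a change in MFR in either direction cannot be attributed to Tafamidis, nor taken to show that Tafamidis has no effect. The mean change with its 95% confidence interval will be reported as the 24-month course under treatment and used to plan a controlled study.*
- In the improvement scenario, replace the claim of confirming a mechanism with a statement that the result would be compatible with one.

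If the full protocol or SAP repeats these readings, make the same edits there. The cost is a few sentences, with no change to patients, data, procedures or tests. The sponsor gives up a negative conclusion, and a firm positive one, that the design could not have supported.
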